##### - Proportion of patients with one or more PIMs stopped at discharge

A mixed-effects logistic regression model will be used for the outcome of stopping 1 or more PIM which controls for intervention, time period, and number of baseline potentially inappropriate medications as fixed effects and cluster as a random effect. This model will be

used to estimate adjusted risk differences. This analysis will be conducted on patients who are taking 1 or more PIM at admission and who are discharged alive from a study unit.

- ER Visit/Readmission within 30-days of hospital discharge

A mixed-effects logistic regression model will be used for the outcome of ER visit or readmission post discharge which controls for intervention, time period, frailty status, long-term care residence, age, gender and number of baseline potentially inappropriate medications as fixed effects and cluster as a random effect. This analysis will be conducted on patients who have consented to, and participated in, the post-discharge follow-up.

- Deaths within 30-days of hospital discharge

A mixed-effects logistic regression model will be used for the outcome of death post discharge which controls for intervention, time period, frailty status, HOMR score and number of baseline potentially inappropriate medications as fixed effects and cluster as a random effect. This analysis will be conducted on patients who have consented to, and participated in, the post-discharge follow-up.

- Falls within 30-days of hospital discharge

A mixed-effects logistic regression model will be used for the outcome of fall post discharge which controls for intervention, time period, frailty status, long-term care residence, age, gender and number of baseline potentially inappropriate medications as fixed effects and cluster as a random effect. This analysis will be conducted on patients who have consented to, and participated in, the post-discharge follow-up.

- Absolute number of medications at discharge

A generalized linear regression model will compare the number of medications at discharge controlling for intervention, time period, and the number of baseline medications as fixed effects and cluster as a random effect. This analysis will be conducted on all patients who are discharged alive on a study unit (see above re transitions of care).

- Absolute number of medications at 30 days post-discharge

A generalized linear regression model will compare the number of medications at 30-days post discharge controlling for intervention, time period, and the number of baseline medications as fixed effects and cluster as a random effect. This analysis will be conducted on patients who have consented to, and participated in, the post-discharge follow-up.

- Absolute number of PIMs at discharge

A generalized linear regression model will compare the number of PIMs at discharge controlling for intervention, time period, and the number of baseline PIMs as fixed effects and cluster as a

random effect. This analysis will be conducted on all patients who are discharged alive on a study unit (see above re transitions of care).

- Proportion of medications that remain deprescribed at 30 days post-discharge

For drugs which were deprescribed at discharge, the proportion which remained prescribed at 30-days (without resuming) will be given for the control and intervention periods without statistical testing. This analysis will be conducted on patients who have consented to, and participated in, the post-discharge follow-up.

- 30-day post-discharge sleep questionnaire responses (Patient-Reported Outcomes Measurement Information System Sleep Disturbance Form 4a)

For individual elements of the score, the number and proportion of each response will be presented in tabular form for pre-hospital and post-hospital results, stratified by intervention for all respondents. The total score will be transformed to a T-score using the standardized table for adults and the median T-scores and interquartile ranges will be presented in tabular form for those respondents who completed both questionnaires and will be stratified by intervention. The Wilcoxon matched pairs sign rank will be used to compare prehospital scores to post discharge scores within intervention and control respectively.

- 30-day self-reported health-related quality of life (EQ-5D-5L and Visual Analog Scale)

Among those who complete the post discharge interview and who are able to provide responses to the EQ-5D-5L questionnaire, the raw scores will be converted into estimates of quality of life using a validated Canadian time-trade off value set. They will be tabulated with median values and interquartile ranges along with the median and IQR for the visual analog scale. A simple comparison between the intervention and control for these measures will use Wilcoxon rank sum.

*Sensitivity analyses as indicated above.*

*9.1b A description of the post-hoc statistical methods to address imbalances between the cluster and the intervention groups*

We performed 5 post-hoc sensitivity analyses to address the low number of clusters in the study: 1) an analysis adjusting for patient factors that differed between groups by  $P < 0.01$ ; 2) treating clusters as a fixed-effect; an analysis with 3) a random and 4) fixed effect for hospital ( $n=11$ , in lieu of cluster) and 5) using permutation, a non-parametric method of evaluating for the weighted within period effect size.

*9.2 The number of subjects planned to be enrolled (sample size calculation)*

The expected proportion of medical patients who will experience an ADE after discharge is between 10 and 19%. For our power calculation we have used the midpoint, 15%. Type

1 error will be 5% and type 2 will be 20%. The cluster correlation expected is no more than 0.03. We wish to show an absolute decrease of four percent. An 8400-patient trial comprising 6 clusters who each recruit 200 patients per cluster-period will have 80% power to detect a change in ADE of from 15% to 11.2% or lower (an absolute risk reduction of 3.8%, number needed to treat 27). Implementation of this power calculation used the Stata function “steppedwedge” and followed the Hussey and Hughes approach.

*Revised prior to the recruitment of the first 200 patients to any cluster to:*

Three clusters will be created based on geographical location in Canada (Quebec, Ontario, Western Canada). These clusters are expected to enroll 500 subjects per time period for a total of 1 baseline and 3 randomized time-periods. The total number of patients will be 6000. With an estimated 15% adverse drug event rate, this will yield at least 80% power to detect an absolute difference of 4.8% (NNT 21) with an alpha of 0.05 and varying intra-cluster correlation ranging from 0.01 to 0.05.

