### *5.2 When and how to withdraw subjects from the trial:*

Withdrawal by participant: Participants will be able to withdraw from the study at any time upon request without penalty. Should participants discontinue, we will request that data accrued to date be retained for analysis but will terminate future follow up. We will also request permission to confirm ER visit, hospitalization, and vital status at day 30 post-hospital discharge.

Withdrawal by investigator: If any clinical adverse event (AE), laboratory abnormality, or other medical condition or situation occurs such that continued participation in the study would not be in the best interest of the participant or interferes with the integrity of the study data. If the participant meets an exclusion criterion (either newly developed or not previously recognized) that precludes further study participation.

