### *5.3 The type and timing of the data to be collected for withdrawn subjects.*

Vital status and hospitalization at 30-days post hospital discharge

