### *5.4 Whether or how subjects are to be replaced:*

433 Not applicable

434

435 *5.5. The follow-up for subjects withdrawn:*

436

437 If they agree, a 2-minute phone call at 30-days post hospital discharge to determine if they  
438 visited the emergency department or were rehospitalized and to determine vital status.

439

440

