#### *Secondary outcomes(s):*

- **Proportion of patients with one or more PIM discontinued at discharge:** determined from the discharge prescription as compared to the best possible medication history performed on admission (medication reconciliation). Medications which have been deliberately tapered to lower doses at discharge will be classified based on a blinded expert review as to whether they constitute “deprescribing”.
- **Absolute number of medications at discharge:** determined from the discharge prescription.
- **Absolute number of PIMs at discharge:** once discharged the MedSafer algorithm will be run on the discharge medication list and PIM status recorded.
- **Adverse drug withdrawal events within 30-days post discharge:** this constitutes a subclass of adverse drug event whereby the adjudicator believes that the patient suffered an adverse event as the consequence of stopping, holding, omitting, decreasing or deprescribing a medication.
- **Absolute number of medications at 30 days post-discharge:** determined from post-discharge interview and review of medications.
  - **Proportion of medications that remain deprescribed at 30 days post-discharge:** determined by asking patients if they have restarted medications which were classified as being deprescribed at discharge.
- **Adverse events within 30-days post discharge:** determined by review of the post-discharge interview.
  - **30-day readmissions (ER or hospitalization) within 30-days post discharge:** a subset of adverse events related to emergency room visit or unplanned readmission to hospital. Details abstracted from the admission note and the death certificate/discharge summary.
  - **30-day mortality in those that survive to hospital discharge:** a subset of adverse events related to death (either in hospital or not in hospital). Where patients have died out of hospital, a modified interview of next of kin will be performed to obtain basic details about the death and this will be adjudicated. Where patients have been readmitted prior to death,
  - **Falls within 30-days of hospital discharge:** based on patient self report at the discharge interview.
- **30-day post-discharge sleep questionnaire responses:** as assessed from the patient interview using the questionnaire.
- **30-day self-reported health-related quality of life:** as assessed from the patient interview using the questionnaire.

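### Thirty-day death and ER visit/readmission are analysed only in follow-up participants, so the status data planned for withdrawn patients appear to enter no analysis

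*Protocol*

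**What the plan says.** Section 9.1a repeats one sentence under ER visit/readmission and under deaths: "This analysis will be conducted on patients who have consented to, and participated in, the post-discharge follow-up".

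Section 5.2 says of patients who withdraw: "we will request that data accrued to date be retained for analysis but will terminate future follow up". It then adds a separate request: "We will also request permission to confirm ER visit, hospitalization, and vital status at day 30 post-hospital discharge". Section 5.3 names the data to be collected for withdrawn subjects: "Vital status and hospitalization at 30-days post hospital discharge"; ER visits are not listed there. Section 5.5 gives the means: "If they agree, a 2-minute phone call at 30-days post hospital discharge to determine if they" went to the emergency department or were rehospitalized, and whether they are alive.

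Section 5.2 also allows withdrawal by the investigator: "If any clinical adverse event (AE), laboratory abnormality, or other medical condition or situation occurs such that continued participation in the study" would be against the patient's interest or would harm the data. That paragraph does not mention 30-day status.

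Section 9 gives withdrawn patients' status data no place in any analysis.

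**The concern.** Death and readmission are objective outcomes. Unlike sleep, quality of life or the adjudicated adverse drug event, they do not need a full patient interview. The protocol recognises this by arranging a short status check for patients who leave the study, and then defines the analysis set so that the result of that check seems not to count.

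If patients outside the set have a different risk from those inside, the reported rates are off. If the share outside, or its relation to outcome, also differs between control and intervention phases, the comparison is off too. For a trial of stopping drugs, these outcomes will be read as evidence on safety, so selection that can be reduced should be.

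**Working it through.** **Step 1: what the text does with a withdrawn patient.** Take a patient who withdraws, agrees to the status check and reports a readmission on the short call.

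- Section 5.2: future follow-up has ended; the status check is a separate permission.
- Sections 5.3 and 5.5: the readmission is recorded.
- Section 9.1a: the analysis takes only patients who took part in follow-up after discharge. On the plain reading this patient is out.

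**Step 2: compare with the protocol's other choices.** Section 9.1a opens with intention to treat as the default unless noted otherwise. Section 9.7 analyses deprescribing at discharge in patients discharged alive, whether or not they complete the interview. The narrower set is therefore a choice made for these outcomes.

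**Step 3: what can be computed.** The protocol states no withdrawal rate, no follow-up participation rate and no 30-day death or readmission rate. The sample size in Section 9.2 concerns adverse drug events and does not bear on this point, so there is no stated figure to reproduce. What follows is an illustration on assumed values.

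Let p be the true rate, equal in both phases (no effect); f the share outside the analysis set; k the event rate outside divided by the rate inside, taken as equal in both phases; and q the rate that is analysed. Then

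p = (1 - f)q + f·k·q, so q = p / (1 + f(k - 1)).

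The false difference, intervention minus control, is

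q_I - q_C = -p(k - 1)(f_I - f_C) / [(1 + f_C(k - 1))(1 + f_I(k - 1))].

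With f_C = 10% and f_I = 20%:

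| Outcome (assumed p) | k | Control q | Intervention q | Difference (points) |
|---|---|---|---|---|
| ER/readmission, 20% | 1.5 | 0.20/1.05 = 19.0% | 0.20/1.10 = 18.2% | -0.9 |
| | 2 | 0.20/1.10 = 18.2% | 0.20/1.20 = 16.7% | -1.5 |
| | 3 | 0.20/1.20 = 16.7% | 0.20/1.40 = 14.3% | -2.4 |
| Death, 5% | 1.5 | 0.05/1.05 = 4.8% | 0.05/1.10 = 4.5% | -0.2 |
| | 2 | 0.05/1.10 = 4.5% | 0.05/1.20 = 4.2% | -0.4 |
| | 3 | 0.05/1.20 = 4.2% | 0.05/1.40 = 3.6% | -0.6 |

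With 10% outside in both phases and k = 2, both phases show 18.2% for readmission and 4.5% for death. The contrast is unbiased and only the levels are too low. If k is below 1, the sign of (k - 1) reverses and so does the bias.

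**Step 4: what the illustration covers.** Here f is everyone outside the set: withdrawn, unreached, and those who consented to data access only (an option in Section 7.2). The planned withdrawal call can recover only the withdrawn patients who agree, so it would remove only part of these differences.

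**The case against.** **The wording may already include them.** Section 9.1a says follow-up, not interview, and the protocol does say interview where it means that, for example for the EQ-5D-5L. The heading of 5.5 itself speaks of follow-up for withdrawn subjects, so a patient who takes the short call could be said to have taken part in follow-up. This stands as far as showing an ambiguity. It does not settle it, because 5.2 says follow-up ends at withdrawal.

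**Detail may sit in a separate analysis plan, and Section 9.5 allows multiple imputation.** True, but Section 9 is itself titled as the statistical analysis plan and fixes the population outcome by outcome. Imputation is a poor substitute for a status that was actually obtained.

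**Patients with events have other routes into the data.** This stands. A reader might infer that a death counts only if next of kin take part, and a survivor only if reached by telephone. The protocol does not support that. In Section 7.1 the kin route ("a modified interview of next of kin will be performed to obtain basic details about the death and this will be adjudicated") is for deaths out of hospital, and readmission details come from hospital documents. The adjudication manual in 7.3 describes a short-form interview completed at readmission.

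**Investigator withdrawal.** A reader might also infer that it removes exactly the patients with events. Section 5.2 requires more than an adverse event, and Section 8.4 keeps patients with adverse events in the 30-day telephone follow-up.

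**Permission is needed.** Also true: the selection can be reduced, not eliminated.

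**Conclusion.** The point holds as a mismatch between what is collected and what is analysed. On the plain reading, the 30-day status of withdrawn patients is gathered and then enters no analysis of death or ER visit/readmission. Sections 5.2 and 5.5 also disagree with 5.3 on whether ER visits are collected.

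The bias has no computable size or direction. The figures above (-0.9 to -2.4 points for readmission, -0.2 to -0.6 for death) rest wholly on assumed event rates, exclusion shares and risk ratios. The contrast bias is zero when exclusion and its relation to outcome are the same in both phases.

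A reader might go further and infer that selection does differ by phase, since Section 4.3(b) keeps sites and patients unaware of the specific objectives until crossover. That makes a difference plausible; nothing in the protocol shows one.

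These are secondary outcomes. The point does not extend to the primary outcome, which needs interview data.

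**What to change.** 1. In Section 9.1a, define the set for death and ER visit/readmission as all consenting patients discharged alive whose 30-day status, event or no event, was ascertained by a planned contact: the 30-day interview, the short-form interview at readmission, the next-of-kin interview or the short withdrawal call. Include patients withdrawn by themselves or by the investigator, where they permit it.
2. Do not add unreached patients merely because a chart shows an event. A chart can reveal a death or readmission but cannot establish that none occurred elsewhere, so this would add events preferentially.
3. Report the number with unknown status by phase, and keep the present set as a sensitivity analysis.
4. State that 5.3 and 5.5 also apply after investigator withdrawal, and align 5.3 with 5.2 and 5.5 on ER visits.

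The withdrawal criteria themselves need no change for this. In particular, removing the provision on newly met exclusion criteria would conflict with Section 5.1.b, which excludes patients ultimately discharged from most non-study units.

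The cost is a few sentences and the use of data already planned. The drawback is that the withdrawal call gives less detail than the full interview.

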## Section 4: Trial Design

*4.1 A specific statement of the primary endpoints and the secondary endpoints, if any, to be measured during the trial.*

*Primary outcome:* Any adverse drug event within 30-days of hospital discharge (as defined by a 5 or 6 on the Leape and Bates scale). ADEs could include adverse drug withdrawal events (ADWEs).

*Secondary outcomes:*

- Proportion of patients with one or more PIM discontinued at discharge
- Absolute number of medications at discharge
- Absolute number of PIMs at discharge
- Adverse drug withdrawal events within 30-days post discharge
- Absolute number of medications at 30 days post-discharge
  - Proportion of medications that remain deprescribed at 30 days post-discharge
- Adverse events within 30-days post discharge
  - 30-day readmissions (ER or hospitalization) within 30-days post discharge
  - 30-day mortality in those that survive to hospital discharge
  - Falls within 30-days of hospital discharge
- 30-day post-discharge sleep questionnaire responses
- 30-day self-reported health-related quality of life

*Sensitivity analyses:*

- Adverse drug events as defined by a 4,5 or 6 on the Leape and Bates scale

*Effect by:*

- Biological sex
- Admission from a long-term care home
- Palliative status
- Frailty status (dichotomized as moderate to severely frail vs not)

*4.2 A description of the type/design of trial to be conducted (e.g., double-blind, placebo-controlled, parallel design) and a schematic diagram of trial design, procedures, and stages.*

This is a cluster randomized trial comprising 3 clusters: Quebec, Ontario, and Western Canada (Alberta and British Columbia).

*4.3 A description of the measures taken to minimize/avoid bias, including:*

(a) Randomization

The order that the cluster enters intervention is randomized prior to the start of the study.

(b) Blinding and Allocation Concealment

Study sites will only learn that they are crossing over to the intervention 4 weeks prior.

Healthcare personnel and patients at participating sites will remain blinded to the specific objectives of the study while in the control phase. They will be aware that we are conducting a study of post-discharge adverse events; however, they will not know that we are specifically looking at medication appropriateness, deprescribing, and adverse drug events. When study sites cross into intervention it will no longer be possible to blind them to the objectives.

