Participants will be phoned within and around 30-days post discharge (day 28-35) and they will have a structured interview to determine their current medication regimen and if it has changed, along with any contact (planned or unplanned) with the healthcare system, and any new or worsening conditions. They will also have the opportunity to report on their quality of sleep (Patient-Reported Outcomes Measurement Information System Sleep Disturbance Form 4a) and quality of life (EQ-5D-5L). All information will be collected in an electronic case file report for later blinded adjudication by an expert in pharmacy, geriatrics, or general internal medicine.

At the time of consent, we will also request access to provincial health insurance data up to one-year post hospital discharge in jurisdictions where available for use in subsequent analyses.

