#### Primary Outcome - Adverse Drug Events

A mixed-effects logistic regression model will be used for the outcome of adverse drug events ( $\geq 5$  on Leape-Bates scale) which controls for intervention, time period, and number of baseline potentially inappropriate medications as fixed effects and cluster as a random effect. This model will be used to estimate adjusted risk differences.

A sensitivity analysis will be conducted (supplemental) using a Leape-Bates Scale of  $\geq 4$  for the definition of adverse drug events.

This analysis will be conducted on patients who have consented to, and participated in, the post-discharge follow-up.

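### EQ-5D-5L and VAS are compared between arms by a pooled rank-sum test that ignores cluster and calendar period, and the sleep analysis gives no treatment contrast

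*Protocol*

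**What the plan says.** Both outcomes are on the secondary list in Section 4.1, where quality of life appears as "30-day self-reported health-related quality of life" directly after the sleep questionnaire.

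- **EQ-5D-5L and VAS (Section 9.1a):** medians and interquartile ranges, then "A simple comparison between the intervention and control for these measures will use Wilcoxon rank sum".
- **Sleep (Section 9.1a):** item tables and median T-scores by arm, then "The Wilcoxon matched pairs sign rank will be used to compare prehospital scores to post discharge scores within intervention and control respectively". No between-arm test or estimate is given.
- **Primary outcome (Section 9.1a):** a mixed logistic model "which controls for intervention, time period, and number of baseline potentially inappropriate medications as fixed effects and cluster as a random effect". All adverse events, PIMs stopped, ER visit or readmission, death, falls, and the medication and PIM counts likewise have period as a fixed and cluster as a random effect.
- **Design (Sections 4.2 and 4.3):** "This is a cluster randomized trial comprising 3 clusters: Quebec, Ontario, and Western Canada (Alberta and British Columbia"), and "The order that the cluster enters intervention is randomized prior to the start of the study".
- **Size (Section 9.2, revised):** "These clusters are expected to enroll 500 subjects per time period for a total of 1 baseline and 3 randomized time-periods", 6000 patients in all.

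Where no test is intended, Section 9.1a says so (withdrawal events; medications that stay deprescribed). It also calls the unadjusted baseline tests descriptive because the trial is cluster randomized. The EQ-5D-5L test carries no such label.

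**The concern.** In a stepped wedge, treatment is tied to calendar time by design. The first period is all control and the last all intervention, and the regions contribute different shares of each arm. A test that pools patients over regions and periods counts regional differences and secular change as treatment effect. It also treats patients within a region as independent, so its standard error is too small.

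At stake is whether a significant or null quality-of-life result can be read as evidence about the tool. As nothing marks the test as descriptive, its p-value would be read against the alpha of 0.05 in Section 9.3. For sleep, a before-after test in each arm does not say whether the arms differ.

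**Working it through.** **Layout.** Three clusters, one baseline and three randomized periods, one cluster crossing at each step. The diagram is not available; this layout is taken from Sections 4.3 and 9.2. It gives 12 cells, 6 control and 6 intervention, and 12 × 500 = 6000 matches the stated total.

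**The plan's own power figure.** The Hussey and Hughes variance is v = I·s·(s + T·τ²) / [(IU − W)·s + (U² + ITU − TW − IV)·τ²]. Here I = 3, T = 4, U = 6, and W = V = 14, so IU − W = 4 and the last bracket is 36 + 72 − 56 − 42 = 10. Take ICC 0.01 and control-rate variance 0.15 × 0.85 = 0.1275. Then τ² = 0.001275, s = 0.99 × 0.1275/500 = 0.000252, v = 0.000295 and SE = 0.0172. Power for 4.8 points is Φ(0.048/0.0172 − 1.96), about 79.9%. The same formula gives 79.9% at ICC 0.03 and 80.6% at 0.05; averaging the two arms' variances gives 85.5% to 86.1%. The stated 80% is reproduced, but by an analysis with period and cluster terms, which the EQ-5D-5L test lacks.

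**Confounding with time.** Mean period is (1×3 + 2×2 + 3×1)/6 = 1.67 for control and (2×1 + 3×2 + 4×3)/6 = 3.33 for intervention. A drift of d per period appears as an effect of (3.33 − 1.67)d = 1.67d.

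**Clustering.** Each region's share of the intervention patients minus its share of the control patients is 3/6 − 1/6 = 1/3, then 0, then −1/3. With total variance 1 and n respondents per cell, the naive variance of the difference is 2/(6n). The true variance is (1 − ICC)·2/(6n) + (2/9)·ICC. Their ratio is R = (1 − ICC) + (2n/3)·ICC, and the false-positive rate is 2Φ(−1.96/√R). This treats the rank-sum test as a comparison of means of a normal outcome.

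No effect and no trend:

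| ICC | R, n = 300 | Rate | R, n = 500 | Rate |
|---|---|---|---|---|
| 0 | 1.00 | 5% | 1.00 | 5% |
| 0.001 | 1.20 | 7% | 1.33 | 9% |
| 0.002 | 1.40 | 10% | 1.66 | 13% |
| 0.01 | 2.99 | 26% | 4.32 | 35% |
| 0.03 | 6.97 | 46% | 10.97 | 55% |
| 0.05 | 10.95 | 55% | 17.62 | 64% |

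**Simulation.** The actual rank-sum test at n = 500, 1000 replicates per setting, gave 4.8%, 34%, 57% and 63% at ICC 0, 0.01, 0.03 and 0.05. At n = 250 it gave 22% (ICC 0.01) and 51% (ICC 0.05). With an assumed drift of 0.05 SD per period and n = 500 it gave 88% even at ICC 0, and 69% to 75% at ICC 0.01 to 0.05. A model with fixed cluster and period effects stayed between 3.8% and 5.9% throughout, with a normal outcome and no cluster-by-period variation.

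**Sleep.** If the true change is equal in both arms and each within-arm test has power p, exactly one is significant with probability 2p(1 − p): 9.5% at p = 0.05 and 50% at p = 0.5. That pattern cannot serve as a treatment contrast.

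**The case against.** Four points deserve weight.

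**The sizes rest on borrowed inputs.** This stands. The protocol gives no ICC, trend or response rate for EQ-5D-5L; 0.01 to 0.05 belongs to the adverse-drug-event calculation. If the true ICC were 0.001 to 0.002 and there were no trend, the rate would be 7% to 13%. The direction of the fault does not depend on the value, but no single inflation figure can be attached to the trial.

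**The sleep tests are not wrong in themselves.** This also stands. A reader might infer that the plan will claim a treatment effect when one arm changes significantly and the other does not. The protocol nowhere says so. Each signed-rank test addresses change within its own arm, and two other secondary outcomes are openly left without a between-arm test. The fair criticism is that no contrast is given and the tests are not labelled descriptive.

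**The missing pre-hospital sleep form.** Section 6.1 mentions sleep only at the follow-up call ("They will also have the opportunity to report on their quality of sleep") and the Section 4.4 schedule lists no such form, so a reader might infer that the paired test has no baseline. The documents do not support that: the schedule names no questionnaire at all, and Section 9.1a provides for respondents who completed both. Only the timing is unstated.

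**Secondary outcomes, described as a simple comparison.** True, and the primary analysis, sample size and power are untouched. But the word simple does not make the test descriptive, and the protocol shows elsewhere that it knows how to apply that label.

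**Conclusion.** The point holds for EQ-5D-5L utility and VAS. The rank-sum test as written does not isolate the intervention from region and calendar period, and it departs from the protocol's treatment of every other tested between-arm outcome. With no effect and no trend, its false-positive rate is about 5% at ICC 0, 26-35% at 0.01 and 55-64% at 0.05. This assumes 300 to 500 respondents per cluster-period, a normal outcome, and the adverse-drug-event ICC range carried over. Any drift adds bias of about 1.67 times the change per period.

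For sleep the conclusion is narrower: the plan yields no treatment contrast and should either supply one or say that the tests are descriptive.

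A reader might also infer that copying the primary model would by itself give correct intervals. With three clusters that is not assured; Section 9.1b added its sensitivity analyses because clusters were few.

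**What to change.** - **EQ-5D-5L utility and VAS:** replace the rank-sum test with a model that has intervention and period as fixed effects plus cluster, as for the other outcomes. Report an adjusted difference with a 95% CI. Add a check suited to three clusters: cluster as a fixed effect, or the within-period permutation method already named in Section 9.1b. If regions are permuted there are only 3! = 6 orders, so that p-value cannot fall below 1/6 (about 0.17); it can check the estimate but cannot reach 0.05.
- **Alternative:** keep medians and interquartile ranges, label them descriptive and give no p-value.
- **Sleep:** fit the same adjusted model to the 30-day T-score with the pre-hospital T-score as covariate, or label the within-arm signed-rank tests descriptive.

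No new patients or data are needed. The price is wider intervals. Because Section 9.1b reports analyses in the past tense, a new model now would be post hoc and should be declared as such under Section 9.6.
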